## **8.5 Reporting of Events**

The study PI has primary responsibility for the safety of participants as it relates to the study protocol. The study coordinator will be responsible for reviewing adverse events and assuring accurate and timely reporting of the adverse events. The co-investigators (including study physician) will review, evaluate and classify adverse events and provide follow-up for events until they are resolved. The DSMB will be responsible for monitoring study data for evidence of adverse effects attributable to participation in the study. The PI will be responsible for reporting study-defined AEs and SAEs to the University of Pittsburgh institutional review board (IRB) according to their timeline and format. The reporting sequence of RAEs will be as follows: trial coordinator, principal investigator, [name] (Study MD), IRB, [name] (DSMB) and [name] (NIA). [name] and [name] will determine which RAEs will be shared with the entire DSMB.

**8.5.1 Serious Adverse Events.** The occurrence of SAEs will be obtained on an Adverse Event form during the 12, 24 and 36 week testing sessions and by any study staff member who learns of a serious event. All study staff will be trained to recognize when there is a SAE and to follow appropriate reporting procedures as they become aware of a reportable event.

SAEs possibly related to the study will be reported to the University of Pittsburgh IRB, the DSMB, and NIA within 24 hours of learning of the event. The expedited report of the SAE will be submitted by telephone, fax, or email. Recognizing that the information available during this 24 hour period may not be sufficient to permit accurate completion of the required adverse event reporting forms, a detailed written SAE report will be completed as soon as the information is available. Follow up information can be requested by the DSMB or the NIA or its representative.

**8.5.2 Unexpected Adverse Event.** An unexpected AE may be witnessed by a member of the research team or a staff member may be told about the occurrence or an

unexpected event that may meet the criteria for reporting. Unexpected AEs that have a potential relationship to study procedures and activities will be reported to the University of Pittsburgh IRB and the DSMB within 24 hours of learning of the event.

**8.5.3 Adverse Events Related or Possibly Related to the Research Intervention.** An AE which in the opinion of the principal investigator, the incident, experience or outcome more likely than not was caused by the procedures involved in the research will be reported to the IRB and the DSMB within 10 working days of the investigator learning of the event. If the AE is serious or unexpected it will be reported as described above.

## **8.6 Follow-up for Adverse Events**

All RAEs will be forwarded to [name] (Independent Safety Monitor – ISM) for adjudication and follow-up. The ISM may contact the study coordinator to request additional information from the participant, significant other, or their health care provider and may seek medical records from a physician or care setting if needed to make a determination about relatedness to the study. If the event is potentially related to the study, the ISM will contact the PI who will consider whether the event was listed in the protocol and consent form and whether modifications to the protocol and consent form should be considered. To ensure the appropriate classification of events, the clinical site physician and/or PI may also be called to review the information. The ISM will be responsible for providing follow-up for ongoing reportable events as follows:

1. The ISM will follow up on RAEs until a final status has been determined for the event. Some RAEs may have a status that is still present at the conclusion of the study. The categories of RAE status are: not recovered/not resolved, recovered/resolved, recovered/resolved with sequelae, recovering/resolving, fatal, unknown.
2. Once the event is no longer ongoing and a final status for the event has been determined, the ISM will record the final status, enter the closed date, and sign and date the report.

### **8.6.1 Action Taken**

The PI, in consultation with the study physician and the ISM, will decide whether or not an RAE requires that the participant be removed from the study intervention. The DSMB will be notified of the recommended course of action. Actions taken in response to the RAE will fall into one of four categories:

- No action taken
- Study procedure interrupted
- Study procedure discontinued
- Study procedure modified

## **8.7 Responsibilities**

The PI has primary responsibility for the safety of participants as it relates to the study protocol. The study coordinator will be responsible for reviewing RAEs and assuring accurate and timely reporting of the RAEs. The study physician and the ISM will review, evaluate, and classify RAEs and provide follow-up for events until they are resolved. The DSMB will be responsible for reviewing and monitoring data for evidence of harm attributable to participation in the study.

#### 8.7.1 Study Physician

The study physician will be available by telephone for consultation with the study personnel during all time periods when participants are engaged in the assessments or interventions. In addition, the study physician will be responsible for reviewing RAEs requiring immediate notification of the IRB and for being “on call” for study related emergencies. We will also obtain the name and contact information for the participant’s primary care physician. In rare cases when the study physician is unavailable, the participant’s primary physician will be contacted.

#### 8.7.2 Independent Safety Monitor (ISM)

[name], the DSMB safety officer will serve as the ISM. The ISM will be responsible for:

- Reviewing reports of RAEs
- Confirming or refuting classification of the event as a RAE
- Requesting additional information as needed in order to make a determination
- Providing the PI with follow-up reports for ongoing RAEs as new information becomes available
- Notifying the PI of final status for the event once it has been determined

#### 8.8 Reporting Expected AEs and RAEs to the DSMB

The DSMB will review tabulated data on non-serious and expected AEs on a semi-annual basis and monitor for adverse event rates out of proportion to those expected. The PI will forward the individual Reportable Adverse Event Records, including a narrative for each event, as well as a table showing all RAEs to the DSMB and NIA semi-annually. The DSMB will review all RAEs that are temporally related to the interventions in aggregate form at its scheduled meetings.

All RAEs that relate to hazards of the study interventions or are cause for urgent concern will be reported to the DSMB chairperson, the NIA and the University of Pittsburgh IRB immediately after recognition of their importance. If the DSMB chairperson concludes that an RAE is of universal and immediate concern, the DSMB chairperson may recommend convening the DSMB to review participant safety based on any individual report or accumulating evidence, including evidence according to treatment assignments.

## 9. **INTERVENTION DISCONTINUATION**

Certain events may result in a temporary interruption or early discontinuation of the trial assessments and interventions or components of these assessments and interventions.

Please refer to the appropriate MOP chapter(s) for specific instructions on stopping criteria during screening, assessment, interventions, and follow-up assessments.

After such events occur, a participant may resume the trial intervention when the study physician and the primary care provider agree that it is appropriate. For mild problems that require temporary cessation of the intervention, the PI in consultation with the study physician and the participant, may agree to reintroduce the participant to the study intervention.

At any time, the DSMB may recommend discontinuation of any component of the intervention or intervention group of the study for any of the following reasons:

1. Compelling evidence from this or any other study of an adverse effect of the study intervention(s) that is sufficient to override the potential benefit of the interventions to the target population
2. Compelling evidence from this or any other study of a significant beneficial effect of the study intervention(s), such that it is continued denial to other study group(s) would be unethical
3. A very low probability of addressing the study goals within a feasible timeframe.

The participants' participation in this research study is completely voluntary. The participant may withdraw, at any time, their consent for participation in this research study. Any identifiable research information recorded for, or resulting from, their participation in this research study prior to the date that they formally withdrew their consent may continue to be used and disclosed by the investigators. To formally withdraw consent for participation in this research study the participant should provide a written and dated notice of this decision to the principal investigator of this research study. If the participant withdraws from the intervention, study staff will ask permission to continue to follow the participant for follow-up assessment. If participation is discontinued for medical reasons and the participant is unable to complete the performance-based testing, all attempts will be made to obtain the self-reported outcomes.

## **10 DATA ANALYSES**

All statistical analyses will be performed using SAS® version 9.3 (SAS Institute, Inc., Cary, North Carolina) based on the **intention-to-treat** philosophy. First, we will evaluate the distributional characteristics of the data set, the prevalence of missing values and general data quality using appropriate descriptive statistics (e.g. mean, median, standard deviation, range, frequencies, percentages) and graphical summarizations (histograms, boxplots, probability plots, scatterplots, lineplots) for all variables for each walk speed stratum for each intervention group for each available time point, as well as change scores from baseline for outcome variables. Second, the baseline pre-intervention values of these variables will be compared between the two intervention arms using independent samples *t*- or Wilcoxon rank sum tests, as appropriate, for continuous variables and a chi-square or Fisher's exact tests, as appropriate, for categorical variables. Although no significant differences are expected

due to randomized treatment assignment and the relatively large sample size, any variables found to be significantly different will be noted and accounted for, by controlling for them as additional covariates in supplements to main analyses. Third, main analyses to address the specific aims and hypotheses will be performed as outlined below. If an analysis of residuals reveals violations of standard assumptions of linear models, we will use a Box-Cox transformation(78) to the response variable before fitting the models. Multiple imputation will be used to account for any missing data in the main analysis.(79, 80) Finally, exploratory follow-up analyses will be performed as outlined below.

### **10.1 Main Analysis.**

First, we will fit a series of linear mixed models using the SAS® MIXED procedure with change from baseline in each of the continuous outcome measures as the dependent variable; intervention arm (standard/standard plus), follow-up time point (12-/24-/36-week) and their interaction as fixed effects of interest; baseline value of outcome as a fixed-effect covariate; and a subject random effect to account for multiple follow-up assessments from the same patients over time and resulting stochastic non-independence of observations. We will appropriately construct means contrasts to compare the two intervention gains at 12 weeks (immediate effect), 24 weeks (delayed effect) and 36 weeks (sustained effect). Test of significance at  $\alpha=0.05$  for gait speed outcome at 12 weeks will be considered the formal test of the primary hypothesis 1.1. Second, we will repeat the above mixed models analysis entirely, but with stratification by baseline gait speed ( $<1.0/1.0+$  m/s). Tests of significance for gait speed outcome at 12 weeks in each of the two strata will be considered formal tests of the primary hypothesis 1.2. Statistical significance of at 24- and 36-week comparisons or other outcomes will be considered as formal tests of the secondary hypotheses involving activity and participation as well as delayed and sustained effects. Third, we will repeat the analyses after controlling for covariates identified a priori or found to be different between intervention arms by including them as additional fixed effects in supplements to main analyses.

### **10.2 Exploratory Analyses.**

To address our subgroup analysis exploratory aim, we will repeat the main analyses after stratification by various other baseline participant characteristics (besides baseline gait speed) to identify, if any, subgroups which are most/least likely to benefit from interventions. A priori, we anticipate that stratification by baseline walking confidence and cognitive function may show differential gains due to the two interventions. We are aware that any definitive subgroup analyses should be supported by strong evidence in the form of a significant interaction effect.(81) Tests of interaction generally have low statistical power, and it is not feasible in the proposed Phase II efficacy trial to recruit the large number of participants required for definitive subgroup analyses beyond the already included pre-planned subgroups based on baseline walking speed. Thus, we will interpret our subgroup analyses with caution and an exploratory rather than a confirmatory philosophy, whose results are to be confirmed in a larger subsequent trial.

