### **10.5 Sample Size Adequacy**

Sample size is estimated based on preliminary data from our pilot studies; our ability to detect statistical significance in two-tailed tests conducted at the  $\alpha=0.05$  level unless otherwise noted; and conservative expected dropout rates of 10, 15 and 20% during the 12-, 24- and 36-week follow-up. Thus, we conservatively anticipate 55, 52 and 49 participants to complete the 12-, 24- and 36-week assessments, respectively. We used standard sample size and power computation methods available in the literature and commercial software (PASS®; Number Cruncher Statistical Systems, Inc., Kaysville, Utah).

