### **Summary of Changes**

There were three unplanned post-completion deviations, all relatively minor or necessary:

- (1) In the subgroup analysis, instead of repeating the main analysis simply stratified by baseline slow/fast stratum, we had included it as an additional fixed effect with interaction terms. This was done so that we could obtain statistical significance of differential findings in the slow and fast strata.
- (2) Actigraphy physical activity variables were analyzed separately with respect to multiple imputation from other outcomes due to they not being required prior to randomization, and the resulting large number without that data.
- (3) Statistical models for actigraphy physical activity variables included wear time as an additional covariate, in keeping with the standard practice in the field.

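### The exploratory subgroup plan asks who benefits most or least but plans no arm-by-subgroup interaction estimate, only separate models within each subgroup

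*Supplement*

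**What the plan says.** Protocol version 1.4, section 1.2, names baseline confidence, physical activity and cognition as exploratory subgroups. Section 10.2 sets the aim of identifying "subgroups which are most/least likely to benefit from interventions" and gives the method: "we will repeat the main analyses after stratification by various other baseline participant characteristics". It singles out walking confidence and cognitive function as likely to show differential gains.

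The same section states that "any definitive subgroup analyses should be supported by strong evidence in the form of a significant interaction effect" and that "Tests of interaction generally have low statistical power". It promises that "we will interpret our subgroup analyses with caution and an exploratory rather than a confirmatory philosophy". It specifies no interaction test or estimate for these subgroups.

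The final statistical analysis plan refers to the published protocol for details. It describes one subgroup analysis, by gait-speed stratum, with stratum and stratum × intervention as added fixed effects. The Summary of Changes explains that "instead of repeating the main analysis simply stratified by baseline slow/fast stratum, we had included it as an additional fixed effect with interaction terms", and gives the reason: "This was done so that we could obtain statistical significance of differential findings in the slow and fast strata". It lists no change for the other subgroups.

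**The concern.** Asking who benefits most or least is asking whether the arm effect differs between subgroups. Fitting the main model separately in each subgroup gives two effects and two p-values, but no estimate of the difference between them and no measure of its uncertainty. When the true effect is the same in both halves, chance and reduced power can make one half reach significance and the other miss it, which is easily taken for a differential response.

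The sponsor gave exactly this kind of reason for moving the gait-speed stratum to an interaction model. It applies equally to confidence, physical activity and cognition. At stake is the reading of the exploratory results, not the primary test.

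**Working it through.** **Inputs.** Section 10.5: two-sided α = 0.05; 55, 52 and 49 completers at 12, 24 and 36 weeks (per arm within a half-sample stratum). Section 10.5.1: SD of change 0.15 m/s, meaningful difference 0.10 m/s, 62 enrolled per arm per stratum. Section 2.4: pilot between-arm differences of 0.11 m/s (PRIME) and 0.07 m/s (RESTORE). The value 0.05 m/s is my assumption, added to show a smaller effect. The documents give no subgroup cut-points, so an even split is assumed.

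**Reproducing the plan's figures.** Two-sample t power for 0.10 m/s with SD 0.15:
- 62 per arm: 95.8% (96.0% by normal approximation); stated 96%.
- 52 per arm: 92.0%; stated 92%.
- 49 per arm: 90.4%; stated 90%.

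The same formula is therefore used below.

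**Disagreement between two equal-effect subgroups.** With power p in each independent half, the chance that exactly one is significant is 2p(1 − p). With 55 per arm in each half:

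| True effect (m/s) | p | 2p(1 − p) |
|---|---|---|
| 0.11 | 0.968 | 0.06 |
| 0.10 | 0.934 | 0.12 |
| 0.07 | 0.679 | 0.44 |
| 0.05 | 0.410 | 0.48 |

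Simulation with 55 per cell gave 12.2%, 43.5% and 48.2% at 0.10, 0.07 and 0.05. The interaction test on the same data was falsely significant in 5.0% to 5.1% of runs.

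**Other outcomes.** The detectable differences in section 10.5.2 are about 0.40 SD (for example 2.2/5.5). With 49 per arm in each half, power is about 0.50, so 2 × 0.50 × 0.50 = 50%.

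**Three moderators on the same people.** The three splits share one overall effect estimate, so their results are not independent. Simulating three unrelated even splits of the same 220 completers gives at least one disagreement in about 23% to 25% of trials at 0.10 m/s, 67% at 0.07 and 73% at 0.05. The like-for-like figure, at least one false positive from three interaction tests, is about 14% (1 − 0.95³ = 0.143).

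**Power of the interaction.** SE = 0.15 × √(4/55) = 0.0405. For a 0.10 m/s difference in effects, 0.10/0.0405 − 1.96 = 0.51, which is power of about 70%. Power is about 41% for 0.07 and 23% for 0.05. A difference of about 0.113 m/s is needed for 80%.

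**The case against.** The strongest reply is that the plan knows all this. It cites the interaction principle, says such tests are weak, calls the analyses exploratory, and leaves confirmation to a larger trial. It states no rule that significance in one subgroup and not the other will count as a differential effect. A reader might infer that rule, but the documents do not contain it, so the percentages above are conditional on it. Stratum-specific estimates can be described without it.

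The effect sizes also matter. At 0.11 and 0.10 m/s the disagreement rate is only 6% and 12%. The 0.07 comes from slow walkers in a pilot whose timing-and-coordination arm had no endurance training. The planned model adjusts for baseline, which would raise power somewhat.

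Three further readings are tempting and unsupported:
- That the results are meant to steer the next trial. The text says only that they are to be confirmed in one.
- That the final analysis plan kept separate models for confidence, physical activity and cognition. It is silent on these subgroups and refers to a publication not shown here; only protocol section 10.2 carries the method.
- That three moderators compound as independent, giving 1 − (1 − x)³ = 33%, 82% and 86%. They split the same participants, so these figures are too high.

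What the reply does not answer is the mismatch between aim and method. An exploratory label limits the strength of a claim; it does not turn two separate estimates into an estimate of their difference. Low power is a reason to show a wide interval, not to leave the comparison out.

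**Conclusion.** The point holds as a minor one. Section 10.2 states an aim about differences in effect and a method that does not estimate them, and the final analysis plan supplies an interaction only for gait-speed stratum. If the separate results were read by significance, the misleading-split rate per moderator runs from close to the 5% of an interaction test at 0.11 m/s to nearly ten times that at 0.05 m/s. It is about 50% for secondary and tertiary outcomes at the plan's own detectable differences. These figures assume even splits, 12-week completers for gait speed (36-week completers for the other outcomes), the stated SDs and an unadjusted comparison. Hypotheses 1.1 and 1.2 and the confirmatory secondary contrasts are not touched.

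**What to change.** For each exploratory moderator, fit one mixed model on all participants that adds moderator and moderator × arm to the main model. Add moderator × time and moderator × arm × time as well, so that the interaction can be estimated at 12 weeks. This goes beyond the final analysis plan's gait-speed model, which names only stratum × intervention. Report the 12-week interaction estimate with its 95% confidence interval, take the subgroup effects from the same model, and label them exploratory. Keeping the moderators as continuous scores is optional; it avoids cut-points but adds a linearity assumption.

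The cost is a few lines of text and some model terms, with no new data. The drawback is the limited power shown above: many intervals will be wide, and a non-significant interaction must not be read as showing equal effects.

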### **10.3 Compliance and Dropout Analyses.**

We will estimate compliance by the number of sessions attended and estimate the proportion of subjects in each group with various levels of compliance. We also will calculate the proportion of subjects missing each session to describe the pattern of compliance. Dropout rates will be calculated as proportions of subjects randomized, and as a cumulative probability of remaining in the study, using survival analysis techniques such as the Kaplan-Meier product-limit estimator. Unlike proportions, the latter statistics, which can be estimated at various times following randomization, take into account when dropouts occur. As with the compliance measure, these statistics will be calculated separately for each treatment group. The information contained in these descriptive analyses may help improve our retention strategies.

